### Reference Committee

In order to monitor specific aspects of the current trial the following Reference Data Monitoring Committee (DMC) will be established. The DMC will be composed of independent experts in the field of radiation oncology, assessing the progress of the trial and available safety data. The mission of the DMC will be to ensure the ethical conduct of the trial and to protect the safety interests of patients.

The DMC will meet on a regular basis, i.e. once a year. Based on its review of available safety data (CRFs) the DMC will provide the sponsor with written recommendations regarding trial modification, continuation or termination.

## Treatment planning and radiation therapy

Patients will be immobilized using a precision head mask to ensure high repositioning accuracy of the target volume and adjacent structures for carbon ion and proton RT. The treatment planning CT (obligate native CT, CT with contrast facultative) and MR-Examination (MRT - compulsory sequences - axial T1 post gadolinium and T2 fat saturated or Flair fat saturated) will be performed in treatment position using the immobilisation device and will be co-registered. The treatment planning CT will consist of continuous 3 mm slices obtained in a stereotactic or virtual simulation set-up.

The delineation of organs at risk and target volume definition will be done on the basis of CTs and MRI scans. The CTV1 should include the GTV (entire residual tumour) and a 1-2 mm safety margin. CTV2 includes the CTV1 with individual safety margin based on surgical and histological reports, and MR-images to account for subclinical disease. The PTV will created adding safety margins around the CTV individually for each patient. The following organs at risk will be defined: eyes, optic nerves, chiasm, brainstem, spinal cord obligatory, temporal lobes, mandible, salivary glands and others facultative. An overlap of the CTV and the OAR needs to be avoided.

### Carbon ion/Proton RT

Carbon ion RT planning is performed using the treatment planning software including biological plan optimization for carbon ions. Two to maximum four irradiation fields will be chosen. At HIT the intensity-controlled raster-scan system will be used for beam application. Considering the tolerance dose to organs at risk a dose of 60 Gy E ± 5% in 19-21 fractions for carbon ions and 70 Gy E ± 5% in 34-36 fractions for protons will be prescribed to the maximum of the calculated dose distribution for the target volume (CTV1). The dose prescription used is related to the isoeffective dose Gy E using daily fractions of 3 Gy E and a weekly fractionation of 4-6 × 3 Gy E for carbon ions. For proton therapy daily fractions of 2 Gy E and a weekly fractionation of 4-6 × 2 Gy E will be used. Treatment planning aims at coverage of the CTV1 and CTV2 with the 95%-isodose line of the prescribed dose.

Evaluation of DVH for the dose distribution will be performed with regards to assess plan quality.

Positioning accuracy will be controlled for each fraction using orthogonal x-rays or cone-beam-CTs. Set-up deviations > 2 mm will be corrected prior to irradiation by correction with the vector of the robotic table.

### Dose constraints to organs at risk for both arms

Dose constraints to organs at risk are estimated considering the experience of our institution as well as the data reported by Emami et al. [17]. The dose to the eyes, temporal lobes, salivary glands, mandible has to be as low as possible. Optic nerves, chiasm and brainstem constraint is ≤ 54 Gy. The brainstem surface (1% of volume) contacting the tumour is allowed to receive >54 Gy, with Dmax ≤ 60 Gy. The doses at the brainstem center has to be <50 Gy. The spinal cord dose constraint is ≤ 45 Gy with 1% of volume allowed to receive >45 Gy (Dmax ≤ 50 Gy).

## Organization and follow-up

Patient data will be collected and documented pseudonymously using electronic data processing (e.g. patient initials, date of birth and study number) at the study office at HIT.

The study data as for example all medical reports, RT documentation and CRF's will be collected at the study office at HIT.

Local recurrences will be confirmed radiologically and histologically whenever possible. At least two medical doctors (radiation oncologist and/or radiologist) will be required to judge of the recurrence or toxicity. Each adverse event occurring in connection with the therapy has to be documented, independent of the cause.

The first and the second follow-up examination will be performed 4-6 weeks and 3 months after completion of RT (follow-up 1 and 2). Follow-up examinations will then be scheduled after 6 months (follow-up 3), 9-12 months (follow-up 4), and then once a year for further 3 years (follow-up 5, 6 and 7). Additional visits will be scheduled as necessary. Acute toxicity is assessed at least weekly during RT and documented at the end of the RT series, 6 weeks after completion of RT and 3 months after RT. Late toxicity will be documented in regular intervals of 6 or 12 months during the observation period. All the patients will be observed for radiation specific acute and late AEs for the time of at least 5 years after irradiation. The maximum grade of toxicity will be determined for each patient.

The Common Terminology Criteria for Adverse Events V4.0 (CTCAE V4.0) will be used to grade acute toxicity from radiation therapy. The criteria are relevant from the 8th irradiation day until day 90, i.e. until the 1st follow-up visit. Thereafter, the RTOG/EORTC Criteria of Late Effects will be utilized. All acute radiation effects will be documented on an Acute Radiation Effect-Form. In addition, the AE-Form and/or SAE-Form will be filled out.

RTOG/EORTC Late Morbidity Scoring Scheme will be used to grade toxicity from radiation therapy occurring later than 90 days after its start, i.e. beyond the 1st follow-up visit. All late radiation effects will be documented on a Late Radiation Effect-Form. Every patient will be followed for LPFS and AEs for a time period of 5 years. Furthermore, patients will be followed for survival and locoregional recurrences for a time period of 5 years after completion of the irradiation.

Accrual period for the trial will be approximately 7 years starting in autumn 2010.

The individual reasons for the study interruption are patient death or the withdrawal of the patient to participate in the study. Withdrawals, lost to follow-ups and patients for whom no event has occurred at study termination are treated as censored observations. The censoring date is given by the last known date at which no event has occurred for the respective patient.

With proven recurrence of disease or the development of distant metastases, the patient will be censored for our study and will be eligible for any additional appropriate therapy or inclusion in other investigative protocols, but should still be followed in order to document survival and radiation specific AEs.

High incidence of unknown AEs or increase in known AEs with the disadvantageous proportion between risk and benefits of the proposed radiation therapy or unacceptable high rates of SAEs can terminate the study earlier.

## Statistical considerations

This trial is a phase III study to demonstrate that ion radiotherapy (experimental treatment) is not relevantly inferior to proton radiotherapy (standard treatment) with respect to the 5 year LPFS rate. The null-hypothesis to be assessed in confirmatory analysis states that the 5 year LPFS rate in the experimental treatment group is at least 5% lower than the 5 year LPFS rate in the standard treatment group. Confirmatory analysis for the primary end point is based on the intention-to-treat population. A group-sequential design is applied with one interim analysis after half of the expected number of events has occurred to allow for an early stopping of the study in case of an overwhelming treatment effect. The stopping rule is according to O'Brien and Fleming [18]. The one-sided critical level in the interim analysis is given by 0.26%, and in the final analysis it is given by 2.4%. Test decision is made by comparing the corresponding repeated confidence intervals to the boundary of the non-inferiority range of -5% (LPFS rate experimental treatment - LPFS rate standard treatment). With this design, the one-sided overall type I error rate is controlled by 2.5%. The confidence intervals for the differences between the LPFS rates are calculated based on the log(-log)-transformed Kaplan-Meier estimates of the rates using Greenwood's formula to estimate the underlying variance [19].

The total sample size of 154 patients provides a power of 80% to show non-inferiority of the experimental treatment to the standard treatment if the experimental treatment is in fact superior with respect to the 5 year LPFS rate by 7% and if the LPFS rate of the standard treatment group is 90%. Calculation of the sample size is based on the non-inferiority test for the differences between rates as described by Farrington and Manning [20].

If the confirmatory aim of the study cannot be reached, the trial still allows a descriptive head-to-head comparison of the two treatments, and the inspection of the confidence interval for the treatment effect enables to exclude a certain amount of difference in efficacy between the treatments.

To assess the impact of major protocol deviations, an analogous analysis of the primary outcome variable will be performed for the per protocol set. Analysis of the secondary endpoints as overall survival, progression-free and metastasis-free survival will be performed analogously to the primary endpoint. The survival curves will be estimated using the Kaplan-Meier product-limit method [21].

All documented variables will be analyzed descriptively by tabulation of the measures of the empirical distributions according to the scale level of the variables. Descriptive p-values of the corresponding statistical tests comparing the treatment groups and associated 95% confidence intervals will be given. The homogeneity of the treatment groups will be described by comparison of the demographic data and the baseline values of the measured variables.

Safety analysis and analysis of toxicity will be based on the data set of all randomized patients who were treated with the experimental or the standard treatment at least once. The safety analysis includes calculation and comparison of frequencies and rates of adverse and serious adverse events reported in the two treatment groups.

All analyses will be done using SAS version 9.1 or higher.

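### The 80% power belongs to the Farrington-Manning test, but the decision rests on a log(-log) Kaplan-Meier interval that cannot be computed if the carbon ion arm has no local recurrence

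*Protocol article*

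**What the plan says.** Everything relevant stands in the Statistical considerations section of the protocol article.

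- Sizing: "The total sample size of 154 patients provides a power of 80% to show non-inferiority", for a proton 5-year LPFS rate of 90% and a carbon ion rate 7 points higher, i.e. 97%. The method is named: "Calculation of the sample size is based on the non-inferiority test for the differences between rates as described by Farrington and Manning".
- Decision: repeated confidence intervals for the difference in 5-year LPFS rates (carbon ion minus proton) are compared with -5%. They are "calculated based on the log(-log)-transformed Kaplan-Meier estimates of the rates", with Greenwood's variance.
- Levels: one-sided 0.26% at the interim, after half the expected events, and 2.4% at the final analysis, for 2.5% overall.

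The article does not give the formula that turns two transformed rates into an interval for their difference. It has no rule for an arm without events. Withdrawals and losses are censored (Primary objectives; Organization and follow-up), but no loss rate is stated.

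**The concern.** The power statement and the decision rule refer to two different procedures. The Farrington-Manning calculation treats each patient as a complete 5-year yes/no outcome. The confirmatory interval works on a transformed Kaplan-Meier rate, and with very few failures it behaves differently.

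The sharpest difference is at zero. If no carbon ion patient has a local recurrence, the Kaplan-Meier estimate is 1, Greenwood's variance is 0 and log(-log 1) does not exist. The most favourable result for carbon ions would then have no computable interval. In an open-label trial, a substitute chosen after seeing such data would be a post-hoc choice of the confirmatory test. The stated 80% also cannot be taken as the power of the stated analysis until the procedure is fully fixed.

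**Working it through.** **Inputs** (Methods/Design for the allocation, otherwise Statistical considerations): proton rate 0.90, carbon ion rate 0.97, margin 0.05, allocation 1:1 with 77 per arm, one-sided 2.5% overall and 2.4% at the final analysis. Loss by year 5 is not stated. I take 0% as the base case and assume 10% and 20% as a range.

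**1. The plan's own figure.** The restricted maximum-likelihood rates with the difference fixed at -0.05 are 0.893 (carbon ion) and 0.943 (proton).

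- Null SD term: √(0.8932×0.1068 + 0.9432×0.0568) = 0.3860
- Alternative SD term: √(0.97×0.03 + 0.90×0.10) = 0.3451
- n per arm = [(1.960×0.3860 + 0.8416×0.3451) / (0.07+0.05)]² = (1.0471/0.12)² = 76.1, rounded up to 77, total 154

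The stated 154 reproduces. At 2.4% the formula gives 77.1 per arm, and 79.9% power with 77. This is the fixed-sample number for complete binary data, with nothing added for loss.

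**2. How often the interval is undefined.** Expected events are 77×0.03 = 2.31 (carbon ion) and 77×0.10 = 7.70 (proton), 10.01 in all.

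- Final analysis: P(no carbon ion event) = 0.97^77 = 0.096.
- Interim, at about 5 events: the carbon ion share of events is 2.31/10.01 = 0.231, so P(none in that arm) ≈ (1-0.231)^5 = 0.27. This is approximate, because it treats the five events as independent draws.

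**3. Power of the stated interval.** The construction is my assumption. Per arm, with S the Kaplan-Meier rate and G the Greenwood sum, the limits are exp(-exp(log(-log S) ± z√G/|log S|)), with z = 1.977. Without censoring, G = (1-S)/(nS). With l and u the lower and upper limits, the lower limit for the difference is

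(S_carbon - S_proton) - √[(S_carbon - l_carbon)² + (u_proton - S_proton)²],

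and non-inferiority is shown if this exceeds -0.05. The no-loss figures come from exact enumeration of the two binomials. The log(-log) figures with loss come from 20,000 simulated trials with constant hazards. The interim was not modelled; spending 0.26% there changes power little.

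| Procedure at 97% v 90% | No loss | 10% loss (assumed) | 20% loss (assumed) |
|---|---|---|---|
| log(-log), undefined = not shown | 70.6% | 64.1% | 58.0% |
| log(-log), exact binomial limit for a zero-event arm | 80.2% | 75.2% | 69.9% |
| log(-log), half-event substitute | 79.2% | not run | not run |
| Trials undefined | 9.6% | 11.1% | 12.0% |
| Farrington-Manning score procedure | 84.8% | 82% | not run |

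The simulation reproduces the no-loss column for log(-log): 70.8%, 80.5% and 9.7% undefined. The score figure with 10% loss comes from a separate 20,000-trial simulation of the score interval on Kaplan-Meier rates, which gave 84.4% without loss.

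The first two rows differ by 80.2 - 70.6 = 9.6 points, which is the share of undefined trials. The low figure and the undefined trials are therefore one defect, not two.

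**4. Actual size at the margin (nominal 2.4%).**

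| True rates, carbon ion v proton | log(-log) | Score | Untransformed Greenwood |
|---|---|---|---|
| 85% v 90% | 1.9% | 2.4% | 2.6-2.7% |
| 89% v 94% | 1.7% | 2.3-2.4% | 3.1% |
| 93% v 98% | 0.3-0.7% | 1.9-2.0% | 4.2% |

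Ranges reflect exact against simulated values or, for log(-log) at 93% v 98%, the zero-event rule.

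**5. The score procedure at zero events.** Even with no event in either arm, the restricted rates are 0.95 and 1. The standard error is √(0.95×0.05/77) = 0.0248 and the statistic is 0.05/0.0248 = 2.01, above 1.977. A decision always exists.

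**The case against.** Planning with a test for rates and analysing censored data by Kaplan-Meier is common, and the article discloses both. It is not a contradiction. This is also a condensed article: the combination formula and a rule for an estimate of 1 are the kind of detail that a full protocol or analysis plan may hold, and the article cites a source for its intervals. That stands. The absence of a zero-event rule here does not prove that none exists.

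A reader might infer that the trial really has only 71% power. The documents do not support this. The figure requires every undefined trial to be scored as a failure, although in those trials carbon ions had no local recurrence and nearly all would show non-inferiority under a sensible rule. It also depends on a construction that the article does not fix. With a zero-event rule and no loss, the stated interval is within about one point of 80%.

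A reader might also infer that more patients are needed, or that the error rate is at risk. Neither follows. The interval is conservative at all three null settings checked, and the loss figures rest on an assumed rate.

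What remains does not depend on unseen detail. The article itself names the sizing test and a different decision interval, and that interval as named has no value in an outcome the plan's assumptions make fairly likely.

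**Conclusion.** The point holds in a limited form and should be fixed; it does not invalidate the design. The 80% was computed for a procedure other than the confirmatory one, and the confirmatory interval is undefined in 9.6% of trials at the final analysis under the plan's own alternative, with a rough 27% at the interim. The 9.6% rests only on the plan's rates, 77 patients per arm and complete follow-up.

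The power figures also rest on the assumed combination of arm-wise limits: 79-80% with a zero-event rule and about 71% without one, falling to about 75% and 64% with an assumed 10% loss. The 80% can therefore be kept for the log(-log) interval only with a zero-event rule and essentially no loss. A procedure matched to the sizing method does better on the same 154 patients.

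**What to change.** Preferred: make the confirmatory repeated interval a Farrington-Manning-type score interval, with variance restricted at the -5% margin, applied to the Kaplan-Meier 5-year rates. Use as effective sample size per arm (1-S)/(S × Greenwood sum), which equals n without censoring, and a size based on the number at risk when an arm has no events. Apply the same rule at both looks and keep the log(-log) intervals as descriptive. The untransformed Greenwood interval is not a safe substitute, since its size reaches 4.2% at 93% v 98%.

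Alternative: keep log(-log), write out how the interval for the difference is built, fix a zero-event rule for the interim and final analyses, and restate the power by simulation of exactly that procedure, including censoring and a stated loss assumption.

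Either way the choice should be made before any comparative data are examined. The cost is a paragraph of text and a short program, with no additional patients.

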## Discussion

Proton therapy is the standard treatment option in skull base chondrosarcoma patients after the tumour resection. Our experience with carbon ion therapy in patients with chondrosarcomas showed excellent results. However, until now, it has been not possible to compare both particles, i.e. protons and carbon ions, directly within the same facility for the treatment of low grade skull base chondrosarcomas.

This trial is a phase III study to demonstrate that carbon ion radiotherapy (experimental treatment) is not relevantly inferior and at least as good as proton radiotherapy (standard treatment) with respect to 5 year LPFS in the treatment of chondrosarcomas. Additionally, we expect less toxicity in the carbon ion treatment arm due to the reduced lateral scattering of the carbon beam.
